#### Process and Outcome Measurement

For both the feasibility study (Study 1) and cluster RCT (Study 2), the primary outcome goal is to reduce emergency department revisits/admissions measured by the proportion of patients who have an emergency department visit or admission within 90 days following discharge. This will be measured via hospital data and patient self-report postintervention. This aligns with the Triple Aim goal of improving population health [24]. Secondary outcomes related to the Triple Aim goal of cost effectiveness are reduction in cost as compared to usual care measured by utilization relative to patient outcomes and experience measured via hospital data as well as patient self-report. Reduction in cost metrics to ascertain cost utility (ie, number of emergency department visits saved; quality-adjusted life years) will be assessed via PROM including QoL measure. Outcomes related to the Triple Aim goal of improved patient experience of care are improved QoL for heart failure patients and improved experience of care (eg, continuity of care, comfort) as measured by the PREM tool. Other population health-related outcomes include reduction in mortality as measured by hospital data and reduction in morbidity as tracked through patient sensor data and self-report.

Primary and secondary outcomes will be identical to the feasibility study. The primary outcome will be whether or not a patient returns to an emergency department, is hospitalized, or dies within 90 days following discharge (60 days of which the patient will be monitored). Utilization data (eg, emergency department visits and admissions) will be assessed by accessing hospital and provincial database records as well as through patient self-reporting of utilization after the study period; the former is the primary method, and the latter will be considered in sensitivity analysis.

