**Methods:**

This 4-year project consists of 3 studies to comprehensively evaluate the outcomes and effectiveness of TEC4Home. Study 1 is a feasibility study with 90 patients recruited from 2 emergency department sites to test implementation and evaluation procedures. Findings from the feasibility study will be used to refine protocols for the larger trial. Study 2 is a cluster randomized controlled trial that will include 30 emergency department sites and 900 patients across British Columbia. The primary outcome of the randomized controlled trial will be emergency department revisits and hospital readmission rates. Secondary outcomes include health care resource utilization/costs, communication between members of the care team, and patient quality of life. Study 3 will run concurrently to study 2 and test the effectiveness of predictive analytic software to detect patient deterioration sooner.

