#### Process and Outcome Measurement

Our primary and secondary outcomes are aligned with the Triple Aim framework (ie, experience of care, population health, and cost/utilization). The primary outcome will be whether or not a patient returns to an emergency department, is hospitalized, or dies within 90 days following discharge. Secondary outcomes are reduction in cost as compared to usual care, improvement of communication during transition of care, quality of life (QoL), patient experience of care, and reductions in mortality and morbidity. Working with the Patient-Centered Performance Measurement and Improvement team in British Columbia, QoL and Patient-Reported Experience Measures (PREM) will be refined during Study 1.

Additionally, patient and health professional experience and satisfaction will be collected via interviews to gather quality improvement information. For health professionals, this will include gathering perspectives on the perceived impact of the home telemonitoring.

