#### Intervention and Control Population

Study hospitals will be selected and matched with control hospitals in pairs based on the 90-day emergency department revisit or hospital admission rate prior to randomization, emergency department staffing (ie, ratio of certified emergency physicians to family physicians in emergency department workforce, number of individual physicians), service area population, and annual number of emergency department visits. One hospital in each pair will be randomly assigned to receive the TEC4Home intervention and the other will remain with usual care. Hospitals will be matched and randomized within each Health Authority in British Columbia, as each Authority will commence the trial at different times according to the size of the population it serves. Sites in Health Authority groupings will enroll in the 18-month study period (in descending order according to size of population served) at the beginning of each subsequent month. At the end of each Authority’s 18-month trial period, emergency departments will participate in an additional total 90 days of monitoring (60 days) and follow-up (30 days) to ensure complete data is gathered for any patients enrolled within the last month of the study period. The intent of this approach is to maximize geographic balance for both equitable opportunity and generalizability purposes. Hospitals for which no appropriate match can be identified will be excluded.

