#### Power and Sample Size

Based on prestudy data, the expected proportion of patients experiencing the primary outcome in the control hospitals is 12% with a standard deviation across hospitals of approximately 2.4%. This SD yields an intraclass correlation coefficient of .005. Based on Ministry of Health/TELUS data from their home monitoring pilot, we expect that the intervention will reduce the proportion of patients with the primary outcome to 6%. If 30 hospitals are included in the study with an average recruitment of 30 patients per hospital (900 patients in total), the study will have a power of 84%, assuming a 2-sided alpha level of .05. We will pair-match hospitals on selected baseline variables and adjust for baseline outcome rates in the analysis to increase the power and to compensate for an intraclass correlation that may be higher than the value used in the calculation. Based on recent Vancouver Coastal Health Authority discharge data, approximately 33 heart failure patients are discharged from the emergency department per 100,000 people per year. Assuming 60% of these patients will be eligible and consent to enroll in the study, 20 patients will be enrolled per 100,000 population per year. We expect that 3 million people will be serviced by the study sites. Over an enrollment period of 18 months, we are confident that we will be able to recruit our planned sample size of 900 patients.

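### The cluster trial's primary outcome is defined once without death and once with it; the two versions disagree on patients who die within 90 days with no intervening ED visit or admission

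*Protocol article*

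**What the plan says.** All references are to the protocol article.

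- **Study 2, Process and Outcome Measurement, first paragraph.** Speaking for both Study 1 and Study 2, it states the primary outcome goal and how it is measured: "the proportion of patients who have an emergency department visit or admission within 90 days following discharge". Death is not a component. The same paragraph lists mortality separately: "Other population health-related outcomes include reduction in mortality as measured by hospital data".
- **Same section, second paragraph.** "Primary and secondary outcomes will be identical to the feasibility study", followed by "The primary outcome will be whether or not a patient returns to an emergency department, is hospitalized, or dies within 90 days following discharge".
- **Study 1, Process and Outcome Measurement.** It gives the version with death, ending "is hospitalized, or dies within 90 days following discharge", and lists mortality again as a secondary outcome.
- **Abstract, Methods.** "The primary outcome of the randomized controlled trial will be emergency department revisits and hospital readmission rates". Death is not mentioned. The project hypothesis under Approach likewise names only ED revisits and admissions.
- **Study 2, Power and Sample Size.** "the expected proportion of patients experiencing the primary outcome in the control hospitals is 12" per cent, expected to fall to 6% with the intervention. The section does not restate what the primary outcome contains.
- **Study 2, Analysis.** It expects few missed outcome events because hospital records supply revisit and admission data. It does not mention deaths.

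**The concern.** A confirmatory trial needs one rule that scores every patient as an event or a non-event. Here two rules stand in adjacent paragraphs.

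They matter for patients who die after discharge with no ED return or admission in between. Without death in the outcome, such a patient is scored the same as one who stayed well. The intervention also works close to this boundary: the Health Professional Communication Pathway section has monitoring clinicians seek advice on ED admission and tells patients with very abnormal readings to go to the ED. Under the version without death, a patient who reaches the ED in time is an event and one who dies at home without contact is not. An arm could therefore look better on the primary outcome for a bad reason.

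Two things follow from the same ambiguity. The planning rates cannot be tied to an endpoint, and the argument that missed events will be rare covers only one of the two versions.

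**Working it through.** **1. Where each version appears**

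| Place | Death a component? |
|---|---|
| Abstract, Methods | No |
| Approach (hypothesis) | No |
| Study 1, Process and Outcome Measurement | Yes |
| Study 2, Power and Sample Size | Not stated |
| Study 2, Process and Outcome Measurement, paragraph 1 | No |
| Study 2, Process and Outcome Measurement, paragraph 2 | Yes |
| Study 2, Analysis (records supplying events) | Only revisits and admissions named |

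The statement that the two studies share outcomes does not settle the matter, because paragraph 1 applies the version without death to Study 1 as well.

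**2. Which patients are scored differently**

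| Course within 90 days | Without death | With death |
|---|---|---|
| ED return or admission, survives | Event | Event |
| ED return or admission, then dies | Event | Event |
| Dies with no ED return or admission | Non-event | Event |
| Neither | Non-event | Non-event |

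Only the third row differs.

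**3. The plan's own power figure**

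Inputs from Power and Sample Size: 12% against 6%; 30 hospitals of 30 patients (450 per arm); ICC 0.005; two-sided alpha 0.05.

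- Design effect = 1 + (30 − 1) × 0.005 = 1.145.
- Effective n per arm = 450 / 1.145 = 393.0.
- SE under the null = √(2 × 0.09 × 0.91 / 393.0) = 0.02042.
- SE under the alternative = √((0.12 × 0.88 + 0.06 × 0.94) / 393.0) = 0.02030.
- Power = Φ((0.06 − 1.96 × 0.02042) / 0.02030) = Φ(0.984) = 83.8%.

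With the unpooled variance throughout, power is 84.0%. The ICC implied by the stated SD is 0.024² / (0.12 × 0.88) = 0.0055, which gives 83.3%. The stated 84% is reproduced. It takes 12% and 6% as given, so it cannot show which version they describe.

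**4. Illustration if 12% and 6% exclude death**

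Let q be the proportion who die with no ED return or admission, assumed equal in both arms. The documents give no value for q, so the values below are assumptions. Each point is 9 of the 900 patients.

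| q | Rates compared | Relative risk | Power |
|---|---|---|---|
| 0 | 12% v 6% | 0.50 | 83.8% |
| 1% | 13% v 7% | 0.54 | 80.2% |
| 2% | 14% v 8% | 0.57 | 76.8% |
| 3% | 15% v 9% | 0.60 | 73.6% |

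The absolute difference stays at 6 points while the variance grows, so power falls by roughly 3 to 4 points for each point of q.

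**5. If 12% and 6% already include death**

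The 84% stands for the composite. If the version without death were then analysed, taking 1, 2 or 3 points equally from both arms gives 87.4%, 91.1% or 94.5%.

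**The case against.** The strongest reply is that the two wordings are not equally formal. Paragraph 1 is introduced as a goal; paragraph 2 is a patient-level definition, agrees with Study 1 and comes with the statement that the outcomes are identical. On this reading the composite with death is operative and the abstract is only shorthand. Part of this stands: the composite is the more explicit wording, which is a reason to keep it. But paragraph 1 also names the measure, the window and the studies it covers, so it works as a definition, and the abstract calls that version the primary outcome.

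Four stronger readings are tempting, and the documents do not support them.

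- **That every death is a success under one version.** A patient who returns to an ED or is admitted and then dies is an event under both.
- **That matching is at fault.** Hospitals are paired partly "based on the 90-day emergency department revisit or hospital admission rate prior to randomization", and the analysis adjusts for a similar prestudy rate. A matching variable or covariate need not equal the endpoint.
- **That the plan lets the outcome be chosen after the data are seen.** Data Collection Procedures allows refinement informed by the feasibility study, and the timeline places refinement of protocols in months 15 to 17, ahead of site enrolment and randomisation in months 18 to 23. Leaving two definitions in place is a risk, not a permission. Mortality is also listed separately, so excess deaths would not be hidden altogether.
- **That the trial has less power than stated.** This requires both that the planning rates exclude death and that deaths add equally to both arms. The documents establish neither.

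**Conclusion.** The contradiction is real and unresolved, and the primary outcome is wrong as written. It is confined to patients who die within 90 days with no ED return or admission, whose number cannot be read from the documents. The uncertainty over 12% and 6% is a consequence of the same defect and not a second error.

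The power arithmetic is sound. The range from about 80% down to 74% is conditional on planning rates that exclude death and on 1 to 3 points of such deaths, equal in both arms. It is no estimate of what the trial will have. Two sources bear on completeness if death is a component: the Analysis section's reassurance about missed events speaks only of revisit and admission records, and mortality is to come from hospital data, which may not capture deaths elsewhere.

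Because the choice determines what the primary analysis counts, it should be settled before randomisation.

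**What to change.** Before the first hospital is randomised:

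1. Use one definition in the Abstract, Approach, both Process and Outcome Measurement sections, Power and Sample Size, and Study 2 Analysis. The composite of ED return, admission or death within 90 days of index discharge is preferable: it is the most explicit wording in the article and does not score deaths without prior contact as successes.
2. Keep ED revisit or admission alone as a secondary outcome.
3. Make sure that the source of death data also captures deaths outside hospital, and extend the statement on missed events to cover them.
4. State whether 12% and 6% include death. If they do not, restate the rates and the power for the composite.

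The cost is protocol wording, one re-run of the power calculation, and a stated power that may fall by a few points.

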#### Health Professional Communication Pathway

Upon discharge of a heart failure patient from the emergency department, emergency physicians will generate an electronic treatment plan that provides updates for the patient and monitoring clinicians. This plan will contain appropriate limits of monitoring criteria (eg, the range of acceptable blood pressure and heart rate, oxygen saturation lower limits, or weight gain or loss per day), and anticipated therapeutic interventions if abnormal results occur.

Patients are requested to submit their data daily between 6:00 AM and midnight. The monitoring clinicians can track a cluster of patients remotely, and if abnormal measurements such as a precipitously low blood pressure occur, an alert will be triggered. The health professionals can then choose one of five actions: take note and continue to monitor the next set of data to determine if the abnormality persists, call the patients to assess directly, send an alert to the patient’s family physician, contact the on-call cardiologist for consultation, or contact an on-call emergency physician to seek advice on management of admission to the emergency department.

It is important to note that in case of health emergencies or very abnormal biometric measurements, patients are instructed to call for help immediately by contacting ambulance services to go to the emergency department and not wait for the monitoring clinician to contact them.

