#### Analysis

We will use descriptive analysis to compare baseline characteristics of emergency departments and individuals. For the primary analysis, an intent-to-treat hierarchical (mixed-effects) logistic regression model will be fit to compare the proportions of patients who experienced the primary outcome in the intervention and control arms. This model will adjust for baseline characteristics at both the emergency department (eg, prestudy emergency department revisit/hospitalization rate, service area population) and patient (eg, age, gender) level. As hospital records will supply emergency department revisit/hospital admission data, missed outcome events will be rare. Monitoring data will be analyzed using statistical process control charting techniques to allow a more comprehensive understanding of patient’s health condition over time.

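### Hospital data are the only named source for death, so deaths outside hospital would be missed for the mortality outcome and, where no ED visit or admission came first, for the composite primary outcome

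*Protocol article*

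**What the plan says.** All places are in the protocol article.

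- **Source for mortality.** Study 2, Process and Outcome Measurement, first paragraph, lists among the other population health outcomes "reduction in mortality as measured by hospital data".
- **Death in the primary outcome.** The second paragraph of that section defines the primary outcome as "whether or not a patient returns to an emergency department, is hospitalized, or dies within 90 days following discharge". The corresponding Study 1 section uses the same definition.
- **Primary outcome without death.** The first paragraph of the Study 2 section instead gives "the proportion of patients who have an emergency department visit or admission within 90 days following discharge".
- **Wider source, for utilization.** The second paragraph states: "Utilization data (eg, emergency department visits and admissions) will be assessed by accessing hospital and provincial database records". Patient self-report of utilization is added for sensitivity analysis.
- **Completeness.** Study 2, Analysis, states: "As hospital records will supply emergency department revisit/hospital admission data, missed outcome events will be rare".
- **Contact with patients.** In the telemonitoring program, "Patients are requested to submit their data daily between 6:00 AM and midnight" (Health Professional Communication Pathway). For the trial arms, "One hospital in each pair will be randomly assigned to receive the TEC4Home intervention and the other will remain with usual care" (Intervention and Control Population).

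**The concern.** The population is aged 65 or older, has heart failure and has been sent home. Some deaths will occur at home or in another place outside hospital. Hospital data need not hold such a death, and the patient cannot report it.

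Two outcomes are affected, to different degrees. For the mortality outcome, any death outside hospital may be lost, even after an earlier readmission. For the composite, only a death with no ED visit or admission before it changes the patient's status, but that patient is then counted as a success. Mortality also enters the planned cost per life year gained (Cost-Effectiveness Evaluation).

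The completeness statement does not close the gap. Its conclusion covers outcome events in general, while its reason covers two of the composite's three components.

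**Working it through.** **1. Sources against outcome components**

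| Component | Named source | Covers events outside hospital? |
|---|---|---|
| ED revisit, admission | Hospital and provincial records; self-report in sensitivity analysis | Not applicable, since these events occur in hospital |
| Death | Hospital data (stated for the mortality outcome; nothing separate for the composite) | No |

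**2. The plan's own power figure** (inputs from Power and Sample Size: 12% against 6%, 30 hospitals of 30 patients, ICC .005, two-sided alpha .05)

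- Design effect = 1 + (30 − 1) × 0.005 = 1.145.
- Effective n per arm = 450 / 1.145 = 393.
- Standard error under the null, with pooled proportion 0.09: √(2 × 0.09 × 0.91 / 393) = 0.02042.
- Standard error under the alternative: √((0.12 × 0.88 + 0.06 × 0.94) / 393) = 0.02030.
- Power = Φ((0.06 − 1.96 × 0.02042) / 0.02030) = Φ(0.984) = 83.8%.

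The stated 84% reproduces. The sample size calculation is not in question.

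**3. Effect of missed deaths on the composite**

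Let q be the share of control patients who die outside hospital within 90 days with no prior ED visit or admission. The article gives no mortality figure, so q is an assumption, taken as 0.5% to 2.5% (450 × q = 2.3 to 11.3 patients). If the same share of events is missed in both arms, the intervention arm loses q/2, because its expected event rate is half as large. The observed rates become 12% − q and 6% − q/2. The power formula of step 2 then gives:

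| q | Control patients | Observed rates | Difference | Power |
|---|---|---|---|---|
| 0 | 0 | 12.0% / 6.0% | 6.0 points | 83.8% |
| 0.5% | 2.3 | 11.5% / 5.75% | 5.75 points | 82.0% |
| 1.0% | 4.5 | 11.0% / 5.5% | 5.5 points | 80.1% |
| 2.0% | 9.0 | 10.0% / 5.0% | 5.0 points | 75.9% |
| 2.5% | 11.3 | 9.5% / 4.75% | 4.75 points | 73.6% |

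**4. Unequal detection, as a hypothetical extreme**

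If such deaths were missed in the control arm only, the observed difference would be 6 − q points: 5.5 at q = 0.5% and 3.5 at q = 2.5%. Power would be 78% and 45%. With no true effect (12% in both arms), the two-sided rejection rate would be about 5.5% and 20% instead of 5%, with the excess showing the intervention as worse. Nothing in the article says that detection will differ in this way.

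**The case against.** **The mortality sentence describes a secondary outcome, and an article may leave the vital-status source to the full protocol.** The first part is correct, and it is why the effect on the composite is conditional. The second part does not remove the point. The article is not silent: it names a source for mortality, and that source undercounts. It also names a wider source in the next paragraph and attaches it to utilization. If the provincial records do include deaths, one sentence would say so.

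**The primary outcome may not include death at all.** This stands as a contradiction in the article. Under the definition without death, the effect on the primary outcome disappears and the effect on the mortality outcome remains.

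**A reader might infer that deaths will be found more completely in the intervention arm, because those patients transmit daily, and so conclude that the comparison is biased.** The documents do not support that conclusion. Hospital data used as the only source apply the same rule to both arms, and no section says that monitoring will be used to establish deaths. Monitoring lasts at most 60 of the 90 days. Both arms complete a poststudy survey, and every enrolled patient must have a family physician who agrees to take part. These contacts are not named as sources for death, but they make it unsafe to assume that a usual-care death at home goes unnoticed. Unequal detection remains possible, since patients and clinicians will know who is monitored. If control deaths were missed more often, the bias would run against the intervention and would not create a false benefit.

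**A reader might also set 0.5 to 2.5 points of misclassification against the 6-point target.** That overstates the harm. If both arms lost the same absolute share, the expected difference would not change. With the same share of events missed, it shrinks by q/2, that is by 0.25 to 1.25 points.

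**Conclusion.** The point holds as under-ascertainment of death. For the mortality outcome it follows directly from the named source. For the composite it depends on death staying in the definition and on patients dying outside hospital with no earlier visit or admission. The assurance that missed events will be rare is sound for revisits and admissions and unsupported for deaths.

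The size cannot be taken from the article. Under the assumed 0.5% to 2.5% of control patients, with the same share of events missed in both arms, power falls from 84% to about 82% to 74%. At the low end the loss is small. Bias between the arms is a possibility inferred from the design and is not part of the conclusion. The point should be corrected before the trial starts, but it does not invalidate the design.

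**What to change.** 1. Reconcile the two definitions of the primary outcome in Study 2, Process and Outcome Measurement, and state one, with or without death.
2. For the mortality outcome, and for the composite if death stays in it, replace hospital data with linked provincial death records through day 90 for every enrolled patient, applied identically in both arms.
3. In Study 2, Analysis, limit the sentence on rare missed events to ED revisits and admissions.

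The cost is an added linkage alongside the provincial records that the trial already intends to access, and a possible reporting lag before deaths are complete. The article does not say whether death records are part of that access, so this needs to be confirmed.
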